**Fig. 1 Fig1:**
[figure not shown]
Target volume delineation and treatment planning: **A** The gross target volume (GTV) is depicted in green and encompassed by the clinical target volume in orange (CTV) with a margin of 3-4 cm in the longitudinal and 1.5-2 cm in the lateral direction. **B** The metallic wire marking the planned surgical incision is delineated and encompassed by a 2 cm margin for skin sparing if possible. **C** Dose distribution using opposing beams, the area of beam entrance was chosen outside of the region destined for surgical incision, treatment was performed with carbon ions

### Proton/carbon ion therapy

Treatment will be administered on an outpatient basis at the Heidelberg Ion-Beam Therapy Center (HIT) [17, 18]. Treatment planning is realized using a treatment planning system (RayStation) that enables conventional and biological optimization. Proton and carbon ion treatment is performed as active beam application (raster scanning method).

### Dose prescription and constraints of critical organs at risk

The prescribed dose to the PTV is 39 Gy (RBE) in 13 fractions (5–6 fractions per week). It is estimated that the α/β value of soft tissue sarcoma is < 10; a consistent value cannot be found in literature. The equivalent photon dose in 2 Gy fractions (EQD2) is in the range of 48.8–42.2 Gy for a α/β = 2–10. There are no risk organs with specific dose constraints to be considered in the extremities.

### Toxicity, safety, and quality of life

Adverse events and toxicity will be reported according to International Common Terminology Criteria for Adverse Events (CTCAE) version 5.0 system. The results of clinical examinations as well as imaging studies (MRI or CT) will be included. Each patient will pass a baseline clinical examination after enrollment. Patients are monitored continuously during treatment, acute adverse events will be documented weekly as well as at the end of treatment. MRI of the according extremity will be planned 3 weeks and the resection 4–6 weeks after the end of radiotherapy. The first clinical follow-up presentation is 6 weeks after resection. Hereinafter all follow-ups include imaging studies and are performed 3, 6, 9, and 12 months after the tumor resection (Table 1). The criteria for feasibility and safety are fulfilled, if the rate of wound healing complications within 120 days after surgery is below 15% and if the therapy was not canceled, unless the reason for canceling is clearly not treatment related.

**Table 1 Tab1:** Time flow of procedures and examinations

	Study inclusion	Prior to RT	During RT	At the end of RT	3 wk. after RT	OP: 4-6 wk. after RT	6 wk. after RT	3 mo. after OP	6 mo. after OP	9 mo. after OP	12 mo. after OP
Inclusion and exclusion criteria	x										
Informed consent	x										
Medical history	x		x	x	x		x	x	x	x	x
Evaluation of symptoms and toxicity	x		x	x	x		x	x	x	x	x
Radiotherapy			x								
Resection						x					
MRI extremities		x			x			x	x	x	x
CT Thorax		x						x	x	x	x
Quality of life (QLQ-C30)		x			x			x			x

Quality of life (QoL) will be assessed by EORTC QLQ-C30 questionnaires. Repetitive completion of the forms is scheduled before treatment, 3 weeks after the end of radiotherapy, 6 months after surgery, and at the end of the study 12 months after surgery. Statistical analysis will be performed after complete acquisition of data. Changes in QoL before and after radiotherapy and before and after surgery will be determined. The two arms of the study will be compared after the end of radiation and at the end of the whole study.

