### Statistical methods

This study is performed to deliver basic data for the neoadjuvant hypofractionated carbon ion or proton radiation treatment of patients with extremity soft tissue sarcoma by providing safety and toxicity data for the here presented treatment regimen. The framework of the safety and feasibility considerations is the current standard neoadjuvant normofractionated photon radiotherapy; it is considered as the historical cohort which served for the planning of this pilot study. The randomization will be performed as block randomization at a ratio of 1:1 aiming at equal group sizes by using a web-based randomization tool (randomizer.at).

Due to the pilot character of the trial, all analyses are performed descriptively and the results are to be interpreted accordingly. The primary endpoint is assessed separately in each of the two treatment groups by applying an optimal adaptive two-stage phase II-design with one interim analysis according to Kunzmann and Kieser [19]. This design is an adaptive variant of Simon’s design [20], where the sample size of stage two is chosen optimally based on the results of the interim analysis. It offers the possibility to prematurely terminate the study due to futility or early success at the timepoint of the interim analysis or allows data-driven recalculation of sample size for the second part of the study while adhering to the specified Type I and Type II error rates. The randomization will be performed as block randomization at a ratio of 1:1. After the interim analysis, dependent on the results, different sample sizes in both treatment arms may be required and the randomization ratio would then be adjusted accordingly. Under the null hypothesis, we would expect in both groups wound complications or dicontinuations to occur in ≥35% of the treated patients within 120 days after surgery, so the expected probability of patients with no wound complications and no discontinuation would be π ≤ 65% for both protons as well as carbon ions. Under the alternative hypothesis, we would expect less than 15% of the patients to have wound complications or discontinue therapy within 120 days after surgery with π ≥ 85% being the rate of patients without wound complications or discontinuation within 120 days after surgery.

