Given these probabilities of success for the alternative and null hypothesis for the protons and carbon ion group, a statistical power of 1-β = 0.80 and a one-sided Type I error rate α = 0.05 for each of the two comparisons, the expected sample size under the null hypothesis is 25.59 and under the alternative hypothesis it amounts to 29.97; the maximum sample size in this design is 52. The interim analysis is performed when the data of 21 patients are available and therefore this is the minimum sample size. The recalculated sample sizes for stage 2 in both treatment arms depend on the patient number with a treatment success (no wound complications and no discontinuation). These values as well as the boundaries for early stopping and the decision boundaries after stage two are calculated according to Kunzmann and Kieser [19] with program code supplied by the authors. The estimation of success rates in both study arms is performed by calculation of point estimators [21] and calculation of two-sided 95%-Clopper-Pearson-type confidence intervals that take the adaptive two-stage design into account [22].

Analysis of the secondary time-to-event endpoints LPFS, DFS, and OS will be performed by the Kaplan–Meier method, patients without event will be censored. The treatment groups are compared using the logrank test. Quality of life will be measured by the EORTC-QLQ30 questionnaire and assessed by presentation of mean, standard deviation, median, minimum, and maximum as well as application of a two-sample t test. For the secondary endpoint local control, absolute and relative frequencies are calculated for each treatment group together with two-sided 95% Agresti–Coull confidence intervals, and an unconditional fourfold table test will be applied for treatment group comparison. Adverse and serious adverse events will be listed, and absolute and relative frequencies will be calculated.

The primary analysis for the primary and secondary endpoints is based on the intention-to-treat set including all study patients fulfilling the inclusion/exclusion criteria and having been treated for at least 1 week. Additionally, a per-protocol analysis is performed as sensitivity analysis which is based on all patients who have received the treatment as planned and for whom the relevant data is available. Safety endpoints are evaluated for all study patients for which the treatment has started.

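### The protocol gives two success criteria for the primary objective, a wound complication rate below 15% and a two-stage test of π ≤ 65%, without saying which governs; the stated 80% power belongs only to the test

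*Protocol article*

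**What the plan says.** The primary objective is the safety and feasibility of the regimen (protocol article, Primary objective). Two places say how it is judged.

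- **Toxicity, safety, and quality of life.** The criteria count as met "if the rate of wound healing complications within 120 days after surgery is below 15% and if the therapy was not canceled", with an exception for cancellations that are clearly unrelated to treatment. The 15% is attached to wound complications; cancellation is a separate clause.
- **Statistical methods.** Each arm is assessed separately by an optimal adaptive two-stage design on a composite success, meaning neither wound complication nor discontinuation. The null is given as "so the expected probability of patients with no wound complications and no discontinuation would be π ≤ 65% for both protons as well as carbon", and the alternative as "with π ≥ 85% being the rate of patients without wound complications or discontinuation within 120 days after surgery". The error rates are "a statistical power of 1-β = 0.80 and a one-sided Type I error rate α = 0.05 for each of the two comparisons". The design figures are "the expected sample size under the null hypothesis is 25.59 and under the alternative hypothesis it amounts to 29.97", and "the maximum sample size in this design is 52", with an interim analysis at 21 patients. Stage 2 sizes, "the boundaries for early stopping and the decision boundaries after stage two" come from published code and are not printed.

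The article does not say how the 15% sentence relates to the test.

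**The concern.** In Statistical methods, 15% failures is the value at which the test is meant to have 80% power. A test planned that way rejects the null at observed failure rates somewhat above the alternative. Under Toxicity, safety, and quality of life, the same 15% serves as the bar for declaring success. If that bar applies to the observed rate, an arm performing exactly as hoped clears it only about half the time, and some arms that reject the null would still not be called safe and feasible.

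The yes-or-no answer to the primary objective would then depend on which section is applied, and the printed power would not describe the conclusion drawn under the 15% sentence. The Discussion part of the abstract names confirmation of safety and feasibility as the aim and foresees a phase III trial afterwards. If the choice is left open until results are seen, it can follow the data.

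**Working it through.** **Inputs (Statistical methods).** p0 = 0.65, p1 = 0.85, power 0.80, first stage n1 = 21, maximum 52, expected sizes 25.59 (null) and 29.97 (alternative), per arm.

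**Step 1: reproduce the printed design.** The boundaries are not printed, so they were reconstructed by searching for the optimal adaptive two-stage binomial design with n1 = 21. Minimising the expected size under the alternative at one-sided α = 0.025 gives:

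| Successes in 21 | Action | Final N | Successes needed |
|---|---|---|---|
| ≤ 15 | stop, futility | 21 | – |
| 16 | continue | 52 | 42 |
| 17 | continue | 38 | 31 |
| 18 | continue | 30 | 25 |
| ≥ 19 | stop, success | 21 | – |

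With X1 ~ Bin(21, π), E[N] = 21 + 31·P(X1=16) + 17·P(X1=17) + 9·P(X1=18).

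- π = 0.65: 21 + 31(0.1085) + 17(0.0593) + 9(0.0245) = 25.59.
- π = 0.85: 21 + 31(0.1147) + 17(0.1912) + 9(0.2408) = 29.97.

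Both expected sizes and the maximum of 52 match the article. The actual type I error is 0.0249. At the printed α = 0.05 with n1 = 21, the optimal designs have a maximum of 31 (minimising the expected size under the null) or 36 (under the alternative), so the printed sizes do not come back.

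**Step 2: compare the two bars at the final N.**

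| N | Most failures with rejection | Most failures below 15% |
|---|---|---|
| 30 | 5 (16.7%) | 4 (13.3%) |
| 38 | 7 (18.4%) | 5 (13.2%) |
| 52 | 10 (19.2%) | 7 (13.5%) |

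After stage 2, every result below 15% also rejects π ≤ 65%. The reverse is not true.

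**Step 3: power at π = 0.85 in this design.** Sum P(X1 = x) × P(final bar reached | x), where P(X1 ≥ 19) = 0.2155 + 0.1221 + 0.0329 = 0.3705.

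- Test alone: 0.3705 + 0.2408(0.8591) + 0.1912(0.7556) + 0.1147(0.6827) = 0.800.
- Test and observed composite failures below 15%: 0.3705 + 0.2408(0.5995) + 0.1912(0.2525) + 0.1147(0.1359) = 0.579.

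The verdicts differ with probability 0.800 − 0.579 = 0.22. The type I error at π = 0.65 falls from 0.025 to 0.012. At higher true success rates the combined rule has power 0.763 (π = 0.88) and 0.866 (π = 0.90).

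**Step 4: apply the 15% to wound complications only.** Hold total failures at 15%, let discontinuations count only through the composite test, and assume how the 15% divides. For wound complication/discontinuation of 13%/2%, 12%/3% and 10%/5%, power is 0.67, 0.71 and 0.765. With no discontinuations it is 0.579. The article gives no such split.

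**Step 5: checks that do not need these boundaries.**

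- For a fixed N and a true 15% rate, P(observed rate < 15%) = P(Bin(N, 0.15) ≤ k), with k the largest count below 15%: 0.61 (N = 21, k = 3), 0.52 (30, 4), 0.49 (38, 5), 0.47 (52, 7).
- In the design that minimises the expected size under the alternative at the printed α = 0.05, power is 0.806 for the test and 0.673 with the 15% requirement. The gap remains under either α.

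**The case against.** The 15% sentence does not say that the rate is the observed one. It stands in a clinical section and resembles the wording of the alternative hypothesis, so it may only restate the target loosely, with Statistical methods holding the decision procedure. On that reading no power is lost. The possibility stands, but criteria that are fulfilled if a condition holds read as a success rule, and nothing in the article tells the reader otherwise.

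The article also calls all analyses descriptive because of the pilot character, and design-adjusted estimates and intervals are reported whichever rule applies. That softens the consequence. It does not remove it, because the same section has the design stop for futility or early success within stated error rates.

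Three stronger inferences are tempting, and the article does not support them:

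- **That the two rules are incompatible.** They are nested after stage 2. Rejection plus a minimum acceptable observed rate is a coherent dual criterion, if it is declared as one.
- **That 18/21 at the interim (14.3% failures) is a contradiction because the design continues.** The 15% sentence sets no interim rule; interim stopping belongs to the two-stage design alone.
- **That power simply is 58%.** That figure needs reconstructed boundaries at α of about 0.025, a true π of exactly 0.85, the raw proportion, and the 15% applied to the composite. The article attaches the 15% to wound complications and does not say how cancellation enters at arm level, so no single power figure follows from its text.

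**Conclusion.** The point holds as a need to reconcile two sections. The article gives two criteria for the primary conclusion and does not say whether one governs or both must be met. Read as a cut-off on the observed rate, the 15% criterion is the stricter, and the stated 80% power does not hold for a conclusion that also requires it.

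The firmest figure is that an arm with a true 15% rate shows less than 15% only about 47% to 61% of the time at N of 21, 30, 38 or 52. This needs no boundaries beyond the choice of those sizes. In the reconstruction that matches the printed sample sizes, power at π = 0.85 falls from 80% to about 58% with the 15% on the composite, and to roughly 67% to 77% under the assumed splits with the 15% on wound complications alone. These figures are conditional on the reconstruction. The direction is not, as the α = 0.05 design shows.

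**What to change.** State one governing success rule, on the composite endpoint, before any arm's result is known, and use it in both sections. Either form is sound, and the choice is the sponsor's:

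1. **Test only.** Success in an arm means that its two-stage test rejects π ≤ 65%. Keep 15% solely as the planning alternative, and report the design-adjusted estimate and confidence interval. The cost is one sentence, and accepting observed failure rates somewhat above 15% as success (up to 10/52, 19.2%, in the reconstructed design).
2. **Test plus the 15% requirement.** Say that both must be met, whether the 15% refers to the raw or the design-adjusted rate, and how discontinuation counts. Restate the power for the combined rule. The cost is the added wording and a lower stated power.

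Neither form changes the two-stage design itself. As the printed sizes reproduce only at α of about 0.025, confirm the α behind the design before restating any power.

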### Secondary endpoints

The effectiveness of treatment is examined by regular MRI of the according extremity and thoracic CT follow-ups. Local control rate depicts the freedom from local progression. Local progression-free survival is defined as the survival probability from the beginning of radiotherapy until local progression. Disease-free survival is defined as the time from the beginning of radiotherapy until local or distant progression. The overall survival is defined as the time from the beginning of radiotherapy until the date of death due to any reason, until the end of the observation period or until the date of the last presentation in case the patient is lost to follow-up (censoring).

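### LPFS and DFS omit death as an event, so with the stated censoring rule both are time-to-progression measures labelled as survival

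*Protocol article*

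**What the plan says.** The section Secondary endpoints of the protocol article gives the definitions.

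- DFS: "Disease-free survival is defined as the time from the beginning of radiotherapy until local or distant progression".
- LPFS: "Local progression-free survival is defined as the survival probability from the beginning of radiotherapy until local progression".
- Local control: "Local control rate depicts the freedom from local progression".
- OS starts at the same point and runs "until the date of death due to any reason", with end of observation and loss to follow-up handled as censoring.

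The Statistical methods section fixes the estimator and the censoring: "Analysis of the secondary time-to-event endpoints LPFS, DFS, and OS will be performed by the Kaplan–Meier method, patients without event will be censored". For the comparison of arms it adds: "The treatment groups are compared using the logrank test".

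Local control is handled separately, as a proportion per arm with a confidence interval and a fourfold table test.

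The section Secondary objectives lists the endpoints and does not add death to LPFS or DFS. No section plans a competing-risk analysis.

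**The concern.** An endpoint called disease-free survival, or local progression-free survival, will be read as the chance of being alive without the event. As defined here, it is the chance of not having progressed, with deaths removed from the count. The article names death where it wants it counted, in OS, and does not name it for the other two.

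LPFS is the more exposed of the two. A patient with distant but no local progression who then dies is censored for LPFS, and censoring by death from the same disease is unlikely to be unrelated to the risk of local progression. For DFS that patient already has an event, so only deaths without any recorded progression are lost.

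LPFS also ends at the same event as local control. The endpoint set therefore describes local progression twice, by different methods, and contains no measure of survival free of local progression.

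At stake is whether the reported curves show what their labels say. The arm comparison is affected too: with deaths censored, the logrank test compares progression rates rather than event-free survival.

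**Working it through.** **1. Is there a stated figure to reproduce?** No. The sample sizes (interim at 21, maximum 52) and error rates in Statistical methods belong to the binary wound-healing endpoint. No event count or power rests on LPFS or DFS.

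**2. What happens to a patient who dies?**

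| Patient | LPFS as written | DFS as written | OS |
|---|---|---|---|
| Dies, no progression | censored at death | censored at death | event |
| Distant progression only, then dies | censored at the latest at death | event at progression | event |
| Local progression, then dies | event at progression | event at progression | event |

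**3. Direction, without assumed rates.** Take follow-up until the defined progression, death or last observation. A death then removes the patient from the risk set at the same time whether it is called censoring or an event, so the numbers at risk are the same. At a time with n at risk, a progressions and b deaths without the defined progression, the Kaplan–Meier factor is

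- as written: 1 − a/n
- death counted: 1 − (a + b)/n

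The second is never larger than the first, and it is smaller whenever b > 0. The curve as written is therefore never below the death-inclusive curve. It lies above it from the first such death on, as long as it has not already reached zero.

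**4. Size, under assumed rates.** The article gives no progression or death rates. Assume constant, independent hazards, with p the risk of progression and d the risk of death without progression by the end of follow-up, each taken as if the other did not act.

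- Deaths censored: S = 1 − p
- Deaths counted: S = (1 − p)(1 − d)
- Gap: (1 − p) × d

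Example with p = 10% and d = 5%: 90.0% against 0.90 × 0.95 = 85.5%, a gap of 4.5 points.

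Gap in percentage points:

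| p | d = 1% | d = 2% | d = 5% | d = 10% |
|---|---|---|---|---|
| 5% | 0.95 | 1.90 | 4.75 | 9.50 |
| 10% | 0.90 | 1.80 | 4.50 | 9.00 |
| 20% | 0.80 | 1.60 | 4.00 | 8.00 |
| 30% | 0.70 | 1.40 | 3.50 | 7.00 |

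**5. Cross-check with observed proportions.** Suppose 15% are seen to progress and 5% die first. Event-free survival is 80%. The total cumulative hazard is −ln 0.80 = 0.2231, the progression share is 0.75 × 0.2231 = 0.1674, and exp(−0.1674) = 84.6%, a gap of 4.6 points. With 10% dying first: −ln 0.75 = 0.2877, 0.6 × 0.2877 = 0.1726, and exp(−0.1726) = 84.1% against 75%, a gap of 9.1 points. Both lie inside the range in step 4.

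**6. In patients.** Among 52 patients, 1–10% is about 0.5 to 5 deaths. Among 21 it is about 0.2 to 2.

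**The case against.** **The effect may be small.** Patients have resectable or marginally resectable disease without nodal or distant metastases, a Karnofsky index of at least 70%, and 12 months of follow-up. Deaths without progression may be few or absent. If 21 to 52 is read as the size of one arm, the standard error of an 80% estimate is √(0.8 × 0.2/21) = 8.7 points to √(0.8 × 0.2/52) = 5.5 points, more than the gap at 5% deaths. This stands as a limit on size. It does not excuse the definition, because the error has one direction and is avoidable.

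**The definitions are coherent as time to progression.** This also stands. The overstatement exists only relative to the survival that the names announce.

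**The LPFS sentence is loose.** It speaks of a survival probability, so one could argue that death was meant to count. The only end point it names is local progression, however, and the DFS sentence has no such wording. LPFS is the weaker evidence of the two.

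**The analysis plan may settle it.** The article already states event, time origin, estimator and censoring. A plan that added death would contradict it rather than complete it.

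Three stronger readings are tempting and are not supported:

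- A reader might infer that the local-control proportion is also wrong because patients who die count as controlled. The article says: "For the secondary endpoint local control, absolute and relative frequencies are calculated for each treatment group". With m local progressions among n patients all followed to a fixed time or to death, cumulative incidence with death as a competing event is m/n, and its complement is exactly that proportion. Study design and Regular study end give every patient the same planned follow-up, and nothing says that lost patients count as controlled.
- A reader might infer that LPFS is redundant. The event is shared, but LPFS uses time and local control does not.
- A reader might infer that the figures cannot be compared with published series. The documents do not say how those series define the endpoints.

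**Conclusion.** The point holds for DFS and, slightly less firmly, for LPFS. As written, both are time-to-progression measures labelled as survival. That the estimates cannot fall below the death-inclusive ones follows from the definitions and the censoring rule alone. The size rests on assumed rates, since the documents supply none: about 0.7 to 9.5 points over 5–30% progression and 1–10% deaths without progression, with the lower part of the range (0.7 to 1.9 points at 1–2% deaths) plausible for this population and follow-up, and no gap if no such death occurs.

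The consequence is limited. The endpoints are secondary, and Statistical methods calls all analyses descriptive. No sample size, stopping boundary or success criterion uses them, and OS, which counts every death, is reported alongside. The definitions should be corrected, but the primary conclusion is not in doubt. No change to the analysis of local control follows from this point.

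**What to change.** Redefine the two endpoints in the protocol and carry the same wording into the analysis plan:

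- LPFS: time from the start of radiotherapy to local progression or death from any cause, whichever comes first.
- DFS: time from the start of radiotherapy to local or distant progression or death from any cause, whichever comes first.

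Patients alive without the event are then censored at their last assessment. Kaplan–Meier and the logrank test stay as planned. If time to progression is what is wanted, the names should say so instead.

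The cost is a wording change. OS already requires dates of death, so no new data are needed, and the sample size does not change. The downside is that reported LPFS and DFS may be slightly less favourable.

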**Methods:**

Extrem-ion is a prospective, randomized, monocentric phase II trial. Patients with resectable or marginally resectable, histologically confirmed soft tissue sarcoma of the extremities will be randomized between neoadjuvant proton or neoadjuvant carbon ion radiotherapy in active scanning beam application technique (39 Gy [relative biological effectiveness, RBE] in 13 fractions [5–6 fractions per week] in each arm). The primary objective is the proportion of therapies without wound healing disorder the first 120 days after surgery or discontinuation of treatment for any reason related to the treatment. The secondary endpoints of the study consist of local control, local progression-free survival, disease-free survival, overall survival, and quality of life.

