### Regular study end

The estimated period of patient accrual is 2 years. The regular end of treatment for the individual patient is 2 to 3 weeks after beginning of radiation therapy (13 fractions, 5–6 fractions per week). The regular study end for each patient is after 12 months after surgery. Patients will be then monitored by regular follow-ups according the current guidelines.

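### LPFS and DFS run from the start of radiotherapy through the resection with progression as the only disease event, so stable tumour left in place is censored as disease-free and pre-operative progression is a permanent failure even after complete removal

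*Protocol article*

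**What the plan says.** The definitions are in the protocol article under Secondary endpoints:

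- **DFS:** "Disease-free survival is defined as the time from the beginning of radiotherapy until local or distant progression".
- **LPFS:** "Local progression-free survival is defined as the survival probability from the beginning of radiotherapy until local progression".
- **Local control:** "Local control rate depicts the freedom from local progression". No time origin and no assessment time point are given.
- **Assessment:** "The effectiveness of treatment is examined by regular MRI of the according extremity and thoracic CT follow-ups".

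The schedule is in the text and Table 1 under Toxicity, safety, and quality of life: "MRI of the according extremity will be planned 3 weeks and the resection 4–6 weeks after the end of radiotherapy". Table 1 also has an extremity MRI before radiotherapy, so the 3-week scan is the first after treatment, not the first on study. After surgery: "Hereinafter all follow-ups include imaging studies and are performed 3, 6, 9, and 12 months after the tumor resection".

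Under Statistical methods, LPFS and DFS are analysed by Kaplan–Meier with event-free patients censored, and the arms are compared by logrank test. Local control is a proportion per arm, compared by a fourfold table test. The main analysis set requires eligibility and at least one week of treatment; it does not require resection. Eligible tumours are "resectable or marginally resectable" (Abstract, Methods).

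**The concern.** LPFS and DFS start while gross tumour is present, continue through its planned removal, and recognise only progression as a disease event. The resection itself has no role in either definition. This gives two doubtful classifications.

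1. A patient with progression on the pre-operative MRI who then has a complete resection and never recurs is a failure for good.
2. A patient whose tumour is not removed, or is grossly left behind, and whose mass stays stable has no event and is censored as disease-free with tumour present.

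The second case is the more serious because the label contradicts the patient's state. It is also not remote by design: marginally resectable tumours are eligible and the analysis set does not depend on surgery.

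The abstract's Discussion announces a phase III trial comparing the two arms on local control, so the pilot's local outcome data are a natural planning input. Rates that mix pre-operative progression with post-operative recurrence, and that do not register failure to clear the tumour, are hard to use for that purpose or to set beside local control rates after resection.

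**Working it through.** The plan gives no figure that depends on these definitions, so there is nothing to reproduce. The check is a reading of the definitions against the schedule, followed by the scale of the effect.

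**Step 1: is there an assessment inside the event window while the tumour is in place?**
- Radiotherapy: "The regular end of treatment for the individual patient is 2 to 3 weeks after beginning of radiation therapy" (Regular study end).
- Resection is 4 to 6 weeks after the end of radiotherapy, so the pre-operative window is 2 + 4 = 6 to 3 + 6 = 9 weeks from the LPFS and DFS origin.
- The post-treatment MRI falls 2 + 3 = 5 to 3 + 3 = 6 weeks from the origin, that is 1 to 3 weeks before surgery.
- Taking 12 months as 52 weeks, the pre-operative share of the time to study end is 6/58 = 10.3% to 9/61 = 14.8%.

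So one scheduled scan lies inside the window before the tumour is removed.

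**Step 2: what happens to each type of patient under the literal wording?**

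| Course | LPFS and DFS as written |
|---|---|
| Progression on pre-operative MRI, complete resection, no recurrence | Event about 5 to 6 weeks from origin |
| No resection, mass stable to 12 months | No event, censored |
| Gross residual tumour, stable to 12 months | No event, censored |
| Complete resection, recurrence later | Event |

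Nothing in the article resets the clock at surgery, exempts growth that is then removed, or makes omitted or grossly incomplete resection an event.

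**Step 3: weight of one reclassified patient.** The Statistical methods section gives a minimum of 21 and a maximum of 52 patients. I read these as per arm, because the design is applied separately in each group.
- 1/21 = 4.8 percentage points
- 1/52 = 1.9 percentage points

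**Step 4: illustration with assumed rates, none of them in the documents.** Let r be the recurrence rate after complete resection, q the share with pre-operative progression who are then completely resected, and u the share with stable tumour left in place for local reasons. Suppose local control is counted from the start of radiotherapy.
- Literal local control = 1 − q − r(1 − q − u)
- Resection-based local control = (1 − u)(1 − r)

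With r = 10%:

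| q | u | Literal | Resection-based |
|---|---|---|---|
| 5% | 0 | 1 − 0.05 − 0.1 × 0.95 = 85.5% | 90.0% |
| 20% | 0 | 1 − 0.20 − 0.1 × 0.80 = 72.0% | 90.0% |
| 0 | 5% | 1 − 0.1 × 0.95 = 90.5% | 0.95 × 0.9 = 85.5% |
| 0 | 10% | 1 − 0.1 × 0.90 = 91.0% | 0.90 × 0.9 = 81.0% |

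The two errors have opposite signs and need not cancel.

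**The case against.** Several stronger readings are tempting, and the document does not support them.

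- **That all three endpoints start at radiotherapy.** This is stated for LPFS and DFS only. Local control has no origin; counting it from the start of radiotherapy is an inference by analogy with LPFS. Its defect is that origin and time point are unstated.
- **That any enlargement on the 3-week MRI is a failure.** The event is progression. The criterion is not given in this condensed article and may be in the full protocol or analysis plan, so its absence is no finding. A strict criterion could make the first case rare. It would not by itself cure the second, because a stable residual mass does not progress under any ordinary criterion.
- **That the plan declares tumour left in place to be controlled.** It does not say so. The classification follows from the stated event and censoring rule in the absence of any rule for such patients.
- **That pre-operative progression is irrelevant.** The Discussion names less progression before surgery as a possible benefit of the shorter schedule. Recording it from the start of treatment is therefore reasonable, and the origin is the same in both arms.
- **That the arms will be mis-ranked.** A systematic shift would need misclassification to differ between arms, and nothing in the documents shows that. At these sizes a chance imbalance of one or two patients is possible, but that is a weaker statement.
- **That the Background's remark on margins proves the point.** It compares positive with negative margins and says nothing about gross residual tumour.

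Two further objections partly stand. A per-protocol sensitivity analysis of patients treated as planned might remove unresected patients, but the article does not say whether resection is part of that condition, and the main analysis would be unchanged. The endpoints are also secondary and, by the plan's own statement, descriptive.

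**Conclusion.** The concern holds in a limited form. LPFS and DFS have explicit definitions whose literal application classes a patient with stable, unremoved tumour as disease-free, and classes pre-operative progression as a permanent failure even when the tumour is then completely removed. This is a stated rule with a poor result, not a detail left to another document. For local control the firm finding is narrower: no origin or time point is given, and under the stated event stable gross residual tumour is not a failure.

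The size is 4.8 points per reclassified patient at n = 21 and 1.9 points at n = 52, assuming these are per-arm sizes. How many patients are affected cannot be taken from the documents; the rates in the illustration are assumptions. The primary endpoint, the sample size and the two-stage decision rules are untouched. The correction should be made because it is cheap before analysis and because the next trial is to be built on local control.

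**What to change.** Amend the endpoint definitions before analysis:

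1. Keep the start of radiotherapy as origin for LPFS and DFS. State the origin and time point of local control, for example 12 months after surgery.
2. Define the local event in local control, LPFS and the local part of DFS as either (a) local recurrence after macroscopically complete resection, or (b) failure to achieve macroscopically complete resection because of local progression or gross residual tumour, dated at surgery or at the decision not to operate.
3. Where the tumour stays in place for non-local reasons, such as distant metastasis or refusal, count the patient as not disease-free in DFS. Do not count this automatically as a local failure in local control or LPFS.
4. Report pre-operative MRI progression that is followed by complete resection separately, and add a sensitivity analysis that counts it as an event.

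**Cost.** No added patients or scans. Completeness of resection must be recorded for every patient. Table 1 has no entry for pathology or margin status, so the sponsor should confirm that this is collected. Recruitment began in June 2021 (Trial status), so the definitions would change by amendment during the trial; the amendment should be dated and made without reference to outcomes by arm.
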